##### Qualitative data

All focus groups and interviews will be audio-recorded and transcribed, and we will analyse the data using thematic analysis in NVivo. We have chosen thematic analysis as it is a widely used qualitative analysis technique that focuses on identifying and reporting the patterns (themes) within the data [8]. As this approach does not rely on a specific theoretical framework, it enables a detailed exploration of the data. Initially, the main rater will read all transcripts (data immersion), before each transcript is systematically coded. Codes will then be grouped under broad themes. A second rater, blind to the original themes, will also read at least 30% of the transcripts and generate their own key themes. Agreement will be discussed at a consensus meeting.

##### Key feasibility outcomes

The feasibility of moving to a fully powered RCT will be assessed drawing on qualitative feedback from the views of social workers (e.g. Were screening and recruitment protocols acceptable?), clinicians (e.g. Was the intervention manual acceptable? Was the time burden acceptable? Were modifications required to the manual?), and young people and carers (e.g. Were recruitment, randomisation, and assessment protocols acceptable? Was the intervention acceptable?). Feasibility for the future fully powered RCT will also be based on the following key questions:Did at least 50% of targeted social workers have a CRIES-8 completed on at least one young person on their caseload?Were large enough groups able to be recruited within the single site to allow 1:1 randomisation, or were modifications required?Were we able to retain at least 60% of the sample at post-intervention follow-ups in the TRT arm and 50% in the CAU arm?

#### Monitoring

##### Trial steering committee

A trial steering committee has been formed, whose role is to provide oversight and guidance on the trial progress and protocol. Alongside monitoring the progress of the trial, this committee also monitors the rights and well-being of participants. As this is a feasibility pilot trial, a data management committee was deemed unnecessary. However, support for randomisation and input on analyses will be provided by a member of the Bristol Randomised Trials Collaborations Unit.

##### Safeguarding, participant welfare, and monitoring of adverse events

Social workers involved in the trial have existing training in safeguarding and risk management as part of their job, including around talking to young people about adverse or traumatic experiences and mental health. The research team are highly experienced working with vulnerable young people, including young people in care, and have established ethically approved standard operating procedures for working with this group.

Young people may become upset when completing research assessments which ask questions about their mental health and trauma history. Whilst this is generally mild and short-lived, the research team is experienced in managing more significant reactions and has established safeguarding and risk management operating procedures. If a young person does become upset, they will be offered breaks and reminded that they can stop or skip the questions. If the young person is very distressed by the assessment, the research team will follow up with the carer and social worker to ensure they can support the young person and are aware of how they are feeling. The research team will also telephone the young person the next day to follow up on how they are managing. If the assessment reveals that the young person is experiencing severe current suicidal ideations (making them ineligible for the trial), the research team will work with the social worker and CAMHS site to support appropriate referrals. There is also a direct referral route back to the recruitment service.

The intervention is being delivered by mental health practitioners from specialist CAMHS and social care sites who are all experienced and trained in working with this population, safeguarding processes and delivering online support/interventions. Facilitators will receive training on the TRT manual by members of the Children and War Foundation, and ongoing supervision during the trial will be provided by clinical members of the research team. If young people in any arm are still experiencing elevated distress at the follow-up assessment (i.e. CRIES-8 scores remain above the cut-off), they will be referred for mental health support, via their social worker.

Adverse experiences will also be closely monitored and recorded throughout the trial. This includes if a young person’s CRIES-8 score increases by 7 or more points, as well as if there are concerns about increases in self-harm during the trial. Adverse experiences will be reported to the independent trial steering committee and, where appropriate, the ethics committee.

Due to the online delivery format of the intervention, additional safety procedures will be implemented in order to manage risk. This includes ensuring a safe adult (i.e. foster carer, key worker) is available to the young person during and after each session, ensuring the young person is in a safe and private location for the intervention sessions and establishing processes for contacting the young person and/or carer directly if they become very distressed during a session. These requirements will all be reiterated to the young person and their primary carer during the initial individual introductory session where they meet the group facilitators.

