### Participants

#### Inclusion criteria

Aged 10 years, 0 months to 17 years, and 11 monthsClinically elevated PTSS at the initial screening stage, defined by scoring 17 or above on the Child Revised Impact of Events Scale (CRIES-8)In any type of care placement (including foster, kinship, residential or semi-independent care), with the exception of living with a biological parentAccess to appropriate technology and a private space to engage in the online sessions

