#### Measures

##### Eligibility measure

The CRIES-8 [24] is a well-established 8-item screening tool for PTSD. It is validated as a self-report measure for 8 + year-olds, who respond to each item on a 4-point scale: *not at all* (0) *l*, *rarely* (1)*y*, *sometimes* (3), and *often* (5). The measure covers re-experiencing and avoidance symptoms. A score of 17 or above is considered to reflect clinically elevated PTSS [24]. The CRIES-8 has been widely used and validated with multiple groups of trauma-exposed young people (e.g. [28, 31]). In the current study, it will be delivered by the young person’s social worker as part of the site’s routine mental health screening procedures.

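### The 7-point CRIES-8 worsening flag cannot fire from a reference score of 34 or above, so for the highest scorers the absence of a flag says nothing about deterioration

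*Protocol article*

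**What the plan says.** Three parts of the Protocol article bear on this point.

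- **The rule.** Under Safeguarding, participant welfare, and monitoring of adverse events, the recorded adverse experiences include the case where a young person's "CRIES-8 score increases by 7 or more points", "as well as if there are concerns about increases in self-harm during the trial". The list is worded as inclusive, not exhaustive. It does not say which earlier score the rise is measured from. Adverse experiences go to the steering committee and, where appropriate, the ethics committee.
- **The scale.** Under Eligibility measure, the CRIES-8 "is a well-established 8-item screening tool for PTSD", with four response options worth 0, 1, 3 and 5 points. The article does not print the maximum total.
- **Who enters.** Under Inclusion criteria, elevated symptoms are "defined by scoring 17 or above on the Child Revised Impact of Events Scale (CRIES-8") at initial screening. There is no upper limit. Under Secondary clinical outcomes, the CRIES-8 is taken again at every assessment.

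A second CRIES-8 rule appears in the same safeguarding section. It applies to either arm at follow-up and is a rule about level: if "CRIES-8 scores remain above the cut-off), they will be referred for mental health support, via their social worker".

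**The concern.** A fixed-change rule on a bounded scale needs enough room above the reference score for the change to occur. Here a high scorer lacks that room. A participant who moves from 34 to the top of the scale has worsened as far as the instrument can show, and the rule records nothing. A participant who moves from 17 to 24 is recorded.

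The Sample size section gives the monitoring of adverse experiences as one of the purposes for which 50 participants are considered adequate. If the flags are later counted, a zero from a participant who could have been flagged and a zero from one who could not look the same, although only the first is evidence. A definitive trial that took over the rule unchanged would take over the same blind spot.

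**Working it through.** The article states no maximum and no expected number of flags, so there is no figure of its own to reproduce. The check compares the stated rule with the stated scale.

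**Inputs**
- Items: 8, each scored 0, 1, 3 or 5 (Eligibility measure).
- Entry: 17 or above at screening, no upper limit (Inclusion criteria).
- Flag: a rise of at least 7 (Safeguarding section).
- Planned sample: 50, 25 per arm (Sample size).

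**Step 1. Ceiling.** Maximum total = 8 × 5 = 40.

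**Step 2. Highest reference score from which the flag can fire.** 40 − 7 = 33. From 33 the only qualifying later score is 40, which means every item at its maximum. From 34 the largest possible rise is 40 − 34 = 6.

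**Step 3. Attainable scores.** Enumerating all totals of eight items scored 0, 1, 3 or 5 gives every integer from 0 to 36, then 38 and 40. Totals of 37 and 39 cannot occur, because a single item can fall short of its maximum only by 2, 4 or 5 points, and no combination of these makes 1 or 3.

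| Reference score | Largest possible rise | Smallest attainable later score that meets the rule |
|---|---|---|
| 29 | 11 | 36 (rise of 7) |
| 30 | 10 | 38 (rise of 8) |
| 31 | 9 | 38 (rise of 7) |
| 32 | 8 | 40 (rise of 8) |
| 33 | 7 | 40 (rise of 7) |
| 34 | 6 | none |
| 35 | 5 | none |
| 36 | 4 | none |
| 38 | 2 | none |
| 40 | 0 | none |

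Of the 22 attainable totals from 17 to 40, five can never be followed by a qualifying rise. That is a count of score values, not of people.

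**Step 4. Reference score.** The article does not name it. The screening score, the baseline score, a repeated baseline (provided for in the TRT arm when the first session is more than a month after the first one) and the previous assessment are all possible. The choice matters. For a participant who goes 36, 20, 30:
- from the starting score: 30 − 36 = −6, no flag;
- from the previous assessment: 30 − 20 = 10, flag.

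On either reading, a rise from a reference score of 34 or above cannot qualify.

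**Step 5. How many participants.** The article gives no distribution of CRIES-8 scores. Purely as assumptions, shares of 2%, 5%, 10%, 20% and 30% at 34 or above correspond to 1, 2.5, 5, 10 and 15 of 50 (50 × share).

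**Step 6. Other measures already collected.** The self-report CATS symptom scale has 20 items scored 0 to 3, range 0 to 60. The CPSS-I has 20 symptom items scored 0 to 4, range 0 to 80. Both are taken at every assessment (Primary quantitative clinical outcome; Secondary clinical outcomes). As the article describes them, both cover DSM-5 PTSD symptoms, whereas the CRIES-8 covers re-experiencing and avoidance only.

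**The case against.** The strongest reply is that nothing in the article is contradictory. Any fixed-change rule on a bounded scale has a ceiling. The list of triggers is open-ended, so staff may record worsening in a child who starts at 36. The article condenses a fuller protocol that is not shown and that may hold further criteria. Severe cases have other routes: referral of anyone still above the cut-off at follow-up, follow-up after distress at assessments, procedures for distress during sessions, and the self-harm trigger. CATS and CPSS-I scores will be summarised by arm, and the analysis plan says ceiling and floor effects will be explored.

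Much of this stands, and it limits the point to recording and reporting. It does not repair the one quantified rule. The referral rule looks at level: a participant who falls from 38 to 20 and one who rises from 34 to 40 are both referred, and neither is recorded as having deteriorated. Summaries by arm do not identify an individual who worsened. An open-ended list permits a record but does not define one.

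Four stronger readings are tempting, and the article does not support them.
- *The reported worsening rate per arm will be biased downwards.* No such rate is planned. Flags go to the steering committee, and the quantitative analysis section lists no flag rate by arm.
- *The committee will take silence for stability.* That is conjecture; its remit covers participants' rights and well-being in general.
- *Anyone who enters at 34 or above can never be flagged at any time.* This holds only if the rise is measured from the starting score.
- *Selection at 17 or above pushes many participants to the top of the scale.* The cut-off applies to the screening score, no floor is stated for the separate baseline score, and 17 lies below the midpoint of a 0 to 40 scale.

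**Conclusion.** The point holds as a limited defect. The arithmetic is exact and depends only on the item scoring and the threshold printed in the article: a CRIES-8 rise of 7 or more cannot be observed from 34, 35, 36, 38 or 40. Because this is the only numeric worsening rule given, the absence of a flag is uninformative for the participants with the highest scores.

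The number of participants concerned is unknown, and any share quoted is an assumption. A reader might infer that the most symptomatic young people are left unprotected. The article does not support that, since the referral, distress and self-harm routes do not depend on the flag. The gap should be closed because following the rule as written would leave such deterioration unrecorded and the remedy is cheap. It does not threaten the validity of the trial.

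**What to change.** Reconcile the adverse-experience rule in the safeguarding section with the scale described under Eligibility measure:

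1. State which score the rise is measured from, including what applies when a baseline is repeated.
2. When flags are reported to the steering committee or published, give the count over participants whose reference score is 33 or below, and list those at 34 or above separately as unable to trigger the flag.
3. For those at 34 or above, show the steering committee their individual change on the self-report CATS or the CPSS-I. If a level for concern is wanted, the committee sets it in advance; none is proposed here. These scales also have upper limits, so the starting score should be shown beside the change.

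The cost is a sentence or two in the adverse-experience definition, one extra line in the safety table, and a few more cases for the committee to review. No new data are needed.

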#### Data management and confidentiality

All data management procedures follow NHS and University requirements and are GDPR-compliant. Electronic data (e.g. online questionnaires, audio recordings) will be stored on the secure university server in the PI’s secure X:Drive, which is password- and access-restricted. Hard-copy data (e.g. any questionnaires completed on paper) will be stored in a locked cabinet in the PI’s locked university office. Participant data will be collected against a non-identifiable numerical ID, which will link the caregiver and young person reports and follow-up assessments. When any audio is transcribed (i.e. qualitative interviews), any potentially identifiable information will be removed. Data will be stored for 10 years, after which time it will be securely destroyed following university policy.

There will be a single password-protected Excel file which contains identifiable information linked to the participant ID, including child, carer and social worker name and key contact details. This is required for both data management and safeguarding/risk management.

#### Service user involvement

Service user involvement (with young people, carers and service providers) has influenced both the intervention modification and the protocol. Two care-experienced young people gave feedback on the modified case study used in the intervention, to ensure that the language was appropriate, whilst the trial protocol (including inclusion/exclusion criteria) has been designed in close consultation with the social-care and CAMHS sites. Engagement with service users (and providers) has been invaluable to developing a project that acknowledges the complexities of these systems and issues and maximises the chance of a successful trial that would lead to a future definitive RCT. Care experienced young people, carers and service providers will also provide input on any dissemination activities.

#### Dissemination strategy

Findings will be disseminated locally to participants and service providers, and more broadly through at least one publication regarding feasibility outcomes, lay summaries for interested services and organisations (e.g. charities), academic and service-focused conferences and media engagement.

## Discussion

Young people in care have some of the poorest outcomes of any group of youth in the UK, yet there remains uncertainty about how best to treat their psychological needs, particularly using intervention methods that are scalable and feasible for the large number of young people who may benefit from support. This project will assess the feasibility of conducting a definitive multi-site RCT that would evaluate the effectiveness of an easy to disseminate and potentially cost-effective intervention for young people in care with elevated PTSS. Whilst rates of both trauma exposure and PTSD are elevated in this group, there is currently no routine screening of symptoms within the social care system and little consensus around treatment approaches. Yet, if left unaddressed, PTSD can be chronic, debilitating and have a significant impact on a young person’s developmental trajectory.

Assessing the feasibility and acceptability of this programme represents an important first step in testing whether it may be a scalable and ultimately effective intervention for targeting elevated PTSS in young people in care. Young people in care can have more complex and unique needs compared to their peers, including the potential lack of a consistent primary caregiver, making a feasibility and acceptability trial all the more crucial. If deemed to be feasible, acceptable and, later, effective, the potential intervention benefits extend beyond reductions in psychological distress, to potentially include associated improvements in broader functioning, which may stem from reducing disabling PTSS, and improvements in carers’ own sense of competency.

## Trial status

Recruitment for the trial began on 1 August 2020; however, due to COVID-19 and UK government restrictions relating to safe working in this context, the intervention was moved to an online format of delivery in October 2020. No participants were recruited before this date. The estimated end date is 30 April 2022.

## Data Availability

Anonymised quantitative participant data will be made available via an appropriate publicly available repository service. Qualitative participant data (such as interview transcripts) will not be made publicly available, as this could compromise participant anonymity, but may be available from the corresponding author on reasonable request.
